	**Study period**						
	**Enrolment**	**Allocation**	**Post allocation**				**Close-out**
**Time Point**	**–t_**1**_**	**t_**0**_**	**t_**1**_**	**t_**2**_**	**t_**3**_**	**t_**4**_**	**t_**5**_**
**Enrolment**							
Eligibility screen	X						
Informed consent	X						
Allocation		X					
Switch				X			
**Interventions**							
INT							
IPT							
Cogpack							
**Assessments**							
Demographic data	X	X					
Psychopathology			X	X	X	X	X
Psychosocial functionality			X	X	X	X	X
Neurocognition			X	X	X	X	X
Medication			X	X	X	X	X
Safety				X	X		

**Figure 1 F1:**
[figure not shown]
Study flow chart.

### Ethical and Regulatory Considerations

The study will be conducted in Switzerland in accordance with current regulations. The ethics committee of the Canton of Zurich approved the study protocol (BASEC Nr.: 2017- 01351). The study protocol was registered in clinicalTrials.gov (NCT03316664; 17.10.2017). Written informed consent will be obtained from the participants before study enrollment.

### Assessments of Outcomes, Raters

Study measurement and outcomes will be assessed by raters blinded regarding group allocation and treatment of the participants. Raters have a psychology degree and training in research methods. All raters have been systematically trained in the use of the study instruments. To ensure raters are blind to treatment arm, they will have no access to patient or study records beyond the strict requirements for rating.

Furthermore, rating sessions will be conducted outside the ward and treatment facilities. In the case of a participant revealing treatment arm allocation to the rater this will be documented. Following the completion of the study, such violations of blinding will be analyzed to determine whether they modified the results.

### Assessment of Outcome, Instruments

Primary outcomes are change in symptom load as measured by the Positive and Negative Syndrome Scale (PANSS) (39), in level of functioning as assessed by the MINI ICF- APP (40) and performance in the Matrics Cognitive Consensus Battery (MCCB) (32). Other outcomes of interest are symptoms and complaints as measured by the Brief Symptom Inventory (BSI) (41), overall severity (or improvement) as measured by the Clinical Global Impression (CGI) (42) scales, overall functionality as measured by the Global Assessment of Functioning (GAF) (43), along with overall mental health as measured by the Health of the Nation Outcome Scales (HoNOS) (44). An overview of the outcome measurements is given in Table 4. Besides these measurement instruments, basic demographic, and clinical characteristics together with medication will also be collected.

**Table 4 T4:** Outcome measurements.

**Test instrument**	**Description**
Positive and Negative Syndrome Scale (PANSS)	The PANSS is a semi-structured interview designed to measure the severity of psychopathology in adult patients with a psychotic disorder, mainly schizophrenia and schizoaffective disorder (39, 45). It measures symptoms in three domains, positive (seven Items), negative (seven items), and general-non-specific symptoms (16 items). Each item is rated on a seven-point Likert scale: from 1 (not present), and from 2 (present) to 7 (very severe). The PANSS range is from 30 to 210 (39).
Mini ICF—APP	The Mini-ICF-APP was developed (40), as a short observer-rated scale for assessing the level of functioning according to the International Classification of Functioning, Disability, and Health (ICF). It assesses 13 domains of functioning, with anchor definitions provided in the manual. Each item is rated on a five-point Likert scale from 0 (no disability) to 4 (total disability).
MATRICS Consensus Cognitive Battery (MCCB)	The MATRICS (Measurement and Treatment Research to Improve Cognition in Schizophrenia) Consensus Cognitive Battery was developed to provide a relatively brief evaluation of key cognitive domains relevant to schizophrenia and related disorders (46). The test Battery includes 10 tests which represent seven different cognitive domains; the test battery is administered as a unit in a standard order. To facilitate a valid interpretation of test scores psychometric properties and normative data were also analyzed (47).
Clinical Global Impression (CGI)	The CGI scale is a brief, easy to use and pragmatic tool for the assessment of psychiatric illness severity and changes over time (42, 48, 49). The CGI consists of three subscales: 1. Severity of Illness (CGI-S), 2. Global Improvement (CGI-I), and 3. Efficacy Index (CGI-E). CGI-S and CGI-I have a seven-point Likert scale response format. It ranges from 1 representing the “healthy subject” to 7 the “extremely ill subject.” The CGI-I ranges from 1 “significant improvement” to 7 “most severe deterioration,” whereby a score of 4 indicates no change. The CGI-E relies on several parameters from whom an index is calculated.
Global Assessment of Functioning (GAF)	The GAF is an observer-rated, 100-point single item scale that rates overall functioning on a continuum from mental health to mental illness (43). The scale ranges from 1 (representing the most impaired individual) to 100 (representing the healthiest individual), divided into (10) deciles, 0 denoting insufficient information to make a judgment.
Health of the Nation Outcome Scales (HoNOS)	The HoNOS is an observer-rated scale and consists of 12 items with a five-point Likert scale response format from 0 (no problems) to 4 (severe/very severe problems). Scores above two are considered clinically significant. The items were combined into four dimensions; each subject can be evaluated on items, subscale scores and the total score (44, 50).

### Statistical Analysis

We calculated our required sample size using G^*^Power 3.1 (51) (ANOVA: Repeated measures, three groups, four measurement points; effect size F = 0.25; < = 0.05; Power = 0.80; number of groups = 3). Based on that calculation, at least 90 participants (30 in each study arm) completing the intervention are required in order to detect small to moderate size differences. Cohen's d (effect size) will be used to compare the percentage of variation in the groups before and after treatment.

All data sets of participants will be analyzed, on an intention to treat basis. Data at baseline, second week and after the intervention, as well as at 6 and 12-months post-intervention will be considered (see Table 3). The demographic and clinical characteristics of the sample will be compared at baseline using an analysis of variance (ANOVA), except for gender and age, which will be assessed using an analysis of covariance (ANCOVA). To compare the overall effect of treatment over time in the three groups, data from the full intent to treat sample will be analyzed using a repeated-measures analysis of variance (ANOVA) with treatment as the intergroup factor and time as the intrasubject factor. *Post-hoc* analyses will be performed using Student's *t*-test for intergroup comparisons. Reported adverse effects and safety-related events will be analyzed separately as will withdrawal from the study or treatment group changes.

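### The power statement assumes four measurement points where the analysis uses five, and claims small-to-moderate sensitivity from a medium effect size (f = 0.25)

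*Protocol article*

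**What the plan says.** All of this stands in the protocol article under Statistical Analysis.

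- The sample size was obtained in G*Power 3.1 with these settings: "Repeated measures, three groups, four measurement points; effect size F = 0.25", a significance level of 0.05 (the symbol is garbled in the text) and power 0.80.
- The conclusion is that "at least 90 participants (30 in each study arm) completing the intervention are required in order to detect small to moderate size differences".
- The next paragraph describes the data to be analysed: "Data at baseline, second week and after the intervention, as well as at 6 and 12-months post-intervention will be considered". That is five occasions. Table 3 also marks five assessment occasions, t1 to t5.
- The main analysis is a repeated-measures ANOVA with treatment between subjects and time within subjects, meant to compare how the three arms fare over time.
- Post-hoc comparisons between arms use Student's t ("test for intergroup comparisons").

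The section does not say which G*Power repeated-measures test was chosen (between factors, within factors, or their interaction) or what correlation among repeated measures was entered.

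**The concern.** Two statements in the section disagree with their neighbours. The calculation counts "four measurement points" and the analysis counts five. The claimed sensitivity reaches below medium, although the only value entered is "effect size F = 0.25"; Cohen's conventional values are 0.10 for small and 0.25 for medium.

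In addition, the required number depends heavily on two settings that are not given, so a reader cannot tell which comparison the 80% power belongs to. This matters when results are interpreted. The Expected Outcomes section predicts differences between particular arms, and a non-significant comparison could be taken as evidence against small or moderate differences that the design had little chance of showing.

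**Working it through.** **Inputs from the section:** k = 3 groups, m = 4 measurement points (5 in the analysis), f = 0.25, alpha = 0.05, power = 0.80, N = 90 completers (30 per arm).

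**Assumptions:** the correlation rho is not stated, so 0.3, 0.5 and 0.7 are shown. Sphericity and G*Power's default effect-size definition are assumed. N is rounded up to a multiple of 3.

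**Formulas (noncentral F):**
- Between groups: lambda = f² × N × m / (1 + (m − 1) × rho), with k − 1 and N − k degrees of freedom.
- Treatment-by-time interaction: lambda = f² × N × m / (1 − rho), with (k − 1)(m − 1) and (N − k)(m − 1) degrees of freedom.

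**Can 90 be reproduced?** Yes, with the between-groups test at a particular correlation. At m = 4 and rho = 0.40, lambda = 0.0625 × 90 × 4 / 2.2 = 10.23 on 2 and 87 degrees of freedom, and power is 81.0%. At rho = 0.41, power is 80.5%. At 0.42 it falls just below 80% and the equal-arm total becomes 93. At rho = 0.5, lambda = 22.5 / 2.5 = 9.0 and power is 75.5%.

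**Total N for 80% power, m = 4, f = 0.25:**

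| Test | rho 0.3 | rho 0.5 | rho 0.7 |
|---|---|---|---|
| Between groups | 78 | 102 | 123 |
| Interaction | 42 | 30 | 21 |

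For the interaction at N = 30 and rho = 0.5, lambda = 0.0625 × 30 × 4 / 0.5 = 15.0 on 6 and 81 degrees of freedom, and power is 80.9%. At N = 90 it exceeds 99%. The interaction figures depend on the effect-size definition: G*Power's alternative options give 78 or 222 at m = 4.

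**Five points instead of four (rho = 0.5):** the between-groups N falls from 102 to 96, and power at N = 90 rises from 75.5% to 77.3%. The interaction N falls from 30 to 27.

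**Sensitivity at N = 90, m = 4, rho = 0.5:**

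| Test | Power at f = 0.10 | f detectable at 80% |
|---|---|---|
| Between groups | 17% | 0.263 |
| Interaction | 47% | 0.139 |

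**Post-hoc t-tests, 30 per arm, two-sided 0.05, one time point (assumed):** noncentrality = d × √(30/2) on 58 degrees of freedom. Power is 80% at d of about 0.74, 48% at d = 0.5 and 12% at d = 0.2. These figures do not involve rho.

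**The case against.** The strongest reply is that nothing here shows 90 to be wrong. A journal article condenses a fuller protocol, and the choice of test and correlation may be recorded there. An undisclosed correlation near 0.40 is plausible and yields exactly 90. That stands: a reader might infer an arithmetic error, but the documents do not support it, because the listed inputs leave the number open rather than contradict it.

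A second reply is that the interaction, under default settings and correlation 0.5, reaches 80% power at f of about 0.14, between small and medium. This also stands, so a flat statement that the trial cannot detect small-to-moderate effects would go too far. It does not rescue the wording as printed, because the section never names the interaction as the powered test. If the interaction was the target, f = 0.25 would not lead to 90 under the default definition. If the between-groups test was the target, it averages over all occasions, baseline included, which is not the change over time that the primary outcomes describe.

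A third reply is that the t-tests are labelled post-hoc and the 80% was never claimed for them. That is correct, and their low power is not a failed promise. It still belongs beside the sensitivity claim, because the arm-against-arm expectations in Expected Outcomes will be read from such comparisons.

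Finally, the mismatch in measurement points works slightly in the trial's favour. That is accepted.

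**Conclusion.** The point holds as an inconsistency in the power statement, not as a proven miscalculation. Two things are wrong as written and need no assumption beyond Cohen's convention: four measurement points against five, and small-to-moderate sensitivity drawn from a medium effect size.

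The size of the second depends on the test. At f = 0.10 and correlation 0.5 with four points, 90 completers give 17% or 47% power, well short of 80% either way. The stated inputs also leave the required total anywhere from 21 to 123 over correlations 0.3 to 0.7, depending on the test, under sphericity and the default effect definition.

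Two stronger readings should be resisted. One is that the trial is too small because it has five occasions; the fifth occasion lowers the required number or leaves it unchanged. The other is that a total of 30 for the interaction was mistaken for a per-arm figure; the coincidence with 30 per arm is visible, but nothing in the article establishes it.

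**What to change.** Keep 90 completers and rewrite the statement:

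1. Redo the calculation with five measurement points.
2. Name the effect tested (the treatment-by-time interaction, if that is the target), the effect-size definition and the correlation actually assumed.
3. Report the resulting power over a range of correlations. A single figure such as 77% would only put a reviewer's assumed correlation of 0.5 and choice of test in place of the authors' own.
4. Replace the small-to-moderate wording with medium (f = 0.25), or with the detectable f for the named test.
5. Add that post-hoc pairwise t-tests with 30 per arm, at a single time point, have 80% power only for d of about 0.74.

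The cost is text only, with no extra participants and no change to the analysis. The downside is that the stated sensitivity becomes less favourable.

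### Covariance analysis is named for the baseline comparison of gender and age, where it does not fit, and is absent from the outcome model, where the baseline value would add precision

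*Protocol article*

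**What the plan says.** All of the analysis text is in the Statistical Analysis section of the protocol article.

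- Baseline comparison: "The demographic and clinical characteristics of the sample will be compared at baseline using an analysis of variance (ANOVA"), with one exception: "except for gender and age, which will be assessed using an analysis of covariance (ANCOVA"). No covariate is named for that ANCOVA.
- Outcome model: a "repeated-measures analysis of variance (ANOVA) with treatment as the intergroup factor and time as the intrasubject factor".
- Data entering it: "Data at baseline, second week and after the intervention, as well as at 6 and 12-months post-intervention will be considered". Baseline is therefore one of the levels of time.
- Pairwise comparisons: post-hoc "analyses will be performed using Student's *t*-test for intergroup comparisons". No adjustment is mentioned.

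Under Assessment of Outcome, Instruments, the endpoints start from baseline: "Primary outcomes are change in symptom load as measured by the Positive and Negative Syndrome Scale (PANSS"), then level of functioning (mini ICF-APP) and cognitive performance (MCCB). The only adjustment mentioned anywhere is in the Discussion, where medication dose and dose equivalents are to be considered as possible confounders, without a model. The Discussion also moves the baseline of participants who switch arm to the start of their main therapy.

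**The concern.** The baseline sentence cannot be carried out as written. Gender is a category and is not a natural response for ANCOVA. Age is continuous, and ANCOVA without a covariate is just ANOVA. After 1:1:1 randomisation, the null hypothesis behind any such test is true by design, so a small p-value can only be a chance finding.

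The outcome model has the opposite problem. It is the one place where covariance adjustment would help, and it has none. The baseline value of each primary outcome is collected before randomisation and is likely to predict the later values. Using it only as a time level leaves precision unused in comparisons planned on 30 completers per arm. The section also does not say whether the treatment main effect or the treatment-by-time interaction is the test of interest. The main effect averages in the baseline visit, where the arms differ only by chance.

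**Working it through.** The plan gives no figure for this point to reproduce. The basis of the sample size of 90 is a separate matter.

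**Inputs.** From the documents: 30 completers per arm, level 0.05 (taken as two-sided), four measurement points in the sample-size statement. Assumed: SD 1 at every visit, a true difference of 0.5 SD, and a correlation rho between visits, shown over a range.

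**1. Baseline tests.** With m independent tests at 0.05, the chance of at least one p < 0.05 under perfect randomisation is 1 − 0.95^m: 0.40 for m = 10 and 0.64 for m = 20. The documents state neither the number of tests nor their independence, so this is only an illustration. In a simulation of 3 × 30 with 40% in one sex category, an ANOVA F test on gender and a chi-square test each rejected in 5.0% of null samples. For a two-category variable the unsuitable test changes almost nothing.

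**2. One post-baseline visit, two arms.** The variance per participant is 2(1 − rho) for change from baseline and 1 − rho² with baseline as covariate. Their ratio is (1 + rho)/2. Power comes from the noncentral t with noncentrality 0.5/√(2v/30), where v is the variance, on 58 df (change) or 57 df (adjusted).

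| rho | v, change | v, adjusted | ratio | power, change | power, adjusted |
|---|---|---|---|---|---|
| 0.4 | 1.20 | 0.84 | 0.70 | 41% | 55% |
| 0.5 | 1.00 | 0.75 | 0.75 | 48% | 59% |
| 0.6 | 0.80 | 0.64 | 0.80 | 57% | 66% |
| 0.7 | 0.60 | 0.51 | 0.85 | 69% | 76% |
| 0.8 | 0.40 | 0.36 | 0.90 | 85% | 89% |

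At rho 0.5, for example, the noncentrality is 0.5/√(2 × 1.00/30) = 1.94 for change and 0.5/√(2 × 0.75/30) = 2.24 adjusted.

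**3. If the treatment main effect is read.** Take baseline plus three later visits, equal correlations of 0.5, and 0.5 SD at each later visit.

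- Main effect over all four visits: the difference shrinks to 0.5 × 3/4 = 0.375. The variance is (1 + 3 × 0.5)/4 = 0.625 and the noncentrality 0.375/√(2 × 0.625/30) = 1.84. Power is about 44%.
- Mean of the three later visits, baseline-adjusted: the variance is (1 + 2 × 0.5)/3 − 0.5² = 0.417 and the noncentrality 0.5/√(2 × 0.417/30) = 3.00. Power is about 84%.
- Mean of the three later visits minus baseline: the variance is 0.667 + 1 − 2 × 0.5 = 0.667. Power is about 64.5%.

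So, at this correlation, about half of the gap between 44% and 84% comes from averaging baseline into the contrast, and the rest from not using baseline as a covariate.

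**The case against.** The strongest reply is that nothing here makes the planned comparison invalid. Several stronger readings are tempting and are not supported:

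- A reader might infer that the p-values for gender would be invalid. The simulation above says otherwise for a two-category variable.
- A reader might infer that chance imbalances will steer the outcome model. The article states no rule by which a baseline test selects a covariate. The comparison stands alone.
- A reader might infer that baseline outcome values are ignored, or that the comparison is biased. Baseline is a level of time, and the treatment-by-time interaction uses it much like a change score. The loss there is of efficiency only.
- A reader might take the rise from 48% to 59% as the gain for the main analysis. It holds for a single-visit pairwise contrast at rho 0.5. The main analysis is a three-group repeated-measures ANOVA on the full intention-to-treat sample, which exceeds 30 per arm if any drop-outs are replaced.

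Two further points are fair. The authors may have meant gender and age as covariates, although the sentence does not say so. The medication remark in the Discussion also shows that the model sentence may not be the whole adjustment plan, and an article may leave covariate detail to a fuller document. Against that, the article does state the factors of its model and its pairwise test, and neither uses baseline as a covariate. The benefit shrinks as the correlation rises: at rho 0.8 it is about four percentage points.

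**Conclusion.** The point holds as one wording error of little numerical consequence and one avoidable loss of efficiency. ANCOVA for gender and age is unsuitable as written, and the baseline tests are uninformative. The outcome model is valid but does not use the baseline value as a covariate. For a single-visit pairwise contrast, adjustment reduces the variance by 30% to 15% against a change score for rho 0.4 to 0.7, and raises power by about 14 to 7 percentage points for a 0.5 SD difference with 30 per arm. The loss is larger if the treatment main effect is the test read. These sizes rest on an assumed correlation, an assumed effect and equal variances at all visits, none of which the documents give. The change is worth making because the data are already collected.

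**What to change.** 1. Delete the baseline significance tests. Report baseline characteristics by randomised arm, as mean and SD or as n and %.
2. For each primary outcome, model the post-baseline values only, with treatment, visit, treatment-by-visit and the pre-randomisation value of that outcome as covariate. Baseline must leave the time factor. Otherwise it would be both response and covariate. Age and gender may be added if stated in advance.
3. Base the arm contrasts on adjusted means from this model in place of the unadjusted t-tests, and say which contrast is the main one.
4. Reconcile this with the Discussion, which resets baseline for switchers to the start of their main therapy. The comparison of randomised arms needs the value from before randomisation. State whether the reset applies only to the post-hoc analysis of switchers.

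The cost is a few degrees of freedom and a modest rewording of the model. No new data are needed.

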## Methods

### Design

We have designed an 8-week, randomized, controlled, assessor-blind, three-parallel-arm trial for patients diagnosed with a schizophrenic psychosis. All patients with the diagnosis of a schizophrenic psychosis (according to the DSM 5 Diagnostic criteria) are eligible to participate. In order to allow the participation of chronic and low-functioning patients, the inclusion criteria were deliberately broad (see Table 1).

**Table 1 T1:** Inclusion and Exclusion criteria.

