Taking into account the usual length of stay in our unit, together with current recommendations, we have adapted both IPT and INT to 20 session programmes comprising the contents of all modules, whilst respecting the specifications and recommendations of the manuals. Cogpack modules are analogous to those of INT. For an overview of the parallel interventions according to TIDieR (see Table 2).

**Table 2 T2:** Content and chedule of Interventions (ToM: Theory of Mind).

	**IPT**	**INT**	**CGP**
**First Block**	**Module 1**	**Module A**	**Module A**
Sesion 1	Card sorting	Information processing	Information processing
Sesion 2	Verbal concept	Attention/vigilance	Attention
Sesion 3	Verbal concept	Perception of emotions	Attention
Sesion 4	Search strategies	Perception of emotions	Vigilance
**Second Block**	**Module 2**	**Module B**	**Module**
Sesion 1	Information collection	Verbal and visual learning	Verbal and visual learning
Sesion 2	Interpretation and discussion	Memory	Memory
Sesion 3	Interpretation and discussion	Social perception (ToM)	Memory
Sesion 4	Title finding	Social perception (ToM)	Verbal and visual learning
**Third Block**	**Module 3**	**Module C**	**Module C**
Sesion 1	Repetition/paraphrasing	Thinking / problem solving	Thinking / problem solving
Sesion 2	Questions and answers	Problem-solving	Thinking / problem solving
Sesion 3	Asking questions	Problem-solving	Thinking / problem solving
Sesion 4	Focussed communication	Problem-solving	Thinking / problem solving
**Fourth Block**	**Module 4**	**Module C / Module D**	**Module C /Module D**
Sesion 1	Cognitive processing	Social schemata	Thinking / problem solving
Sesion 2	Cognitive Processing	Social schemata	Thinking / problem solving
Sesion 3	Role-playing games	Working memory	Working memory
Sesion 4	Role-playing games	Working memory	Working memory
**Fifth Block**	**Module 5**	**Module D**	**Module D**
Sesion 1	Problem identification	Attribution	Working memory
Sesion 2	Generating solutions	Attribution	Working memory
Sesion 3	Generating solutions	Attribution	Working memory
Sesion 4	Implementing solutions	Emotion regulation	Working memory

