### Randomization and Switch Procedure

Following baseline assessment, patients will be randomly assigned (1:1:1 fashion) to either IPT or INT (active interventions) or Cogpack (control intervention). We expect six to eight participants in each treatment arm. Through randomization, there is the possibility that some participants will experience difficulties with their assigned treatment group. In such cases, patients will be permitted to switch to another treatment arm after 2 weeks. The sole criterion for switching intervention arm is patient preference due to excessive, respectively insufficient demands. We have chosen not to formulate explicit criteria for switching intervention arm for two reasons; first of all to empower patients in their commitment to therapy; second to prevent bias through the delayed selection of participants.

After participation in a minimum of 16 sessions (60–90 min each) in one treatment arm, the intervention will be completed; follow-up assessments will be carried out at 6 and 12 months. For a Study- Flow diagram (see Table 3 and Figure 1).

**Table 3 T3:** Schedule of enrolment, interventions, and assessments.

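### The planned repeated-measures ANOVA relies on sphericity for its treatment-by-time test, which is implausible over five visits spanning about 60 weeks; uncorrected, the error rate could lie between 5% and about 11%

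*Protocol article*

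**What the plan says.** All of the analysis text is in the Statistical Analysis section of the protocol article. The stated purpose is "To compare the overall effect of treatment over time in the three groups", and the stated model is a "repeated-measures analysis of variance (ANOVA) with treatment as the intergroup factor and time as the intrasubject factor". On the visits it says: "Data at baseline, second week and after the intervention, as well as at 6 and 12-months post-intervention will be considered". That makes five measurement occasions.

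The Design section places the post-treatment visit: "We have designed an 8-week, randomized, controlled, assessor-blind, three-parallel-arm trial". The Assessment of Outcome section makes the primary outcomes change in PANSS, change in mini-ICF-APP, and MCCB performance.

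The section names no covariance structure, no check of sphericity and no epsilon correction. It also does not state that the F tests will be used uncorrected. The sample size inputs ("three groups, four measurement points; effect size F = 0.25; < = 0.05; Power = 0.80; number of groups = 3") include neither a correlation between measurements nor an epsilon.

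**The concern.** In a repeated-measures ANOVA the tests involving time (time itself and treatment-by-time) hold their level only if the difference between any two visits has the same variance, whichever two are taken. With similar variances at each visit, this means that all pairs of visits must be equally correlated. Here one pair lies 2 weeks apart within an admission, and another lies about 60 weeks apart, spanning discharge for most patients (the Discussion gives a usual stay of 6 to 8 weeks) and unrestricted drug treatment. Equal correlation over such a range would be surprising.

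The term at risk matters. A between-arm difference in change, which is how two of the three primary outcomes are defined, is the treatment-by-time effect. The main effect of treatment averages over all visits, baseline included, and does not express change. If sphericity fails and nothing is done about it, the treatment-by-time p value is too small for any outcome concerned.

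**Working it through.** **The plan's own figure.** The article states that "at least 90 participants (30 in each study arm) completing the intervention are required". This cannot be reproduced uniquely, because the test family, the correlation and epsilon are not given. With assumed correlation 0.5 and epsilon 1, the between-factors test at four occasions needs 100 patients (102 for equal arms) and the within-between interaction needs 30 in total. About 90 appears with correlation 0.4 for the between-factors test (88, or 90 for equal arms), or with correlation 0 and epsilon 0.5 for the interaction (90). So the sample size does not reveal which effect decides or what covariance was assumed.

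**Inputs from the article.** Three arms at 1:1:1, 30 completers each, five visits. With an 8-week treatment the visits fall at week 0, 2, 8, 8 + 26 = 34 and 8 + 52 = 60. The gaps are 2, 6, 26 and 26 weeks. As a sensitivity case, 20 sessions ("we have adapted both IPT and INT to 20 session programmes") at two a week take 10 weeks and give weeks 0, 2, 10, 36 and 62.

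**Inputs assumed.** The covariance between visits. The article gives none, so a range is shown.

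**Step 1: what sphericity requires.** For visits j and k with common variance σ², Var(Yj − Yk) = 2σ²(1 − ρjk). Take two examples.
- Pure exponential decay with correlation 0.5 at 26 weeks: ρ = 0.5^(2/26) = 0.948 at 2 weeks and 0.5^(60/26) = 0.202 at 60 weeks. The variances of the differences stand in the ratio 0.798/0.052, about 15 to 1.
- Stable patient effect 0.4, serial part 0.4 (same decay), visit noise 0.2: ρ = 0.4 + 0.4 × 0.948 = 0.779 and 0.4 + 0.4 × 0.202 = 0.481. The ratio is 0.519/0.221, about 2.3 to 1.

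**Step 2: from covariance to error rate.** The treatment-by-time test has (3 − 1)(5 − 1) = 8 and (90 − 3)(5 − 1) = 348 degrees of freedom, with a 5% critical value of 1.965. Departure from sphericity is measured by ε = (tr A)² / [4 tr(A²)], where A = C′ΣC and C holds four orthonormal contrasts between visits. Under no effect, F is distributed approximately as F(8ε, 348ε), so the actual error is about P[F(8ε, 348ε) > 1.965]. This was checked by simulation (20,000 null trials per structure, simulation error about 0.15 to 0.2 points).

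| Assumed structure, weeks 0/2/8/34/60 | ε | Approximation | Simulated, uncorrected | Simulated, Greenhouse-Geisser |
|---|---|---|---|---|
| Compound symmetry, ρ = 0.5 | 1.00 | 5.0% | 5.3% | 4.9% |
| Stable 0.5, serial 0.2, noise 0.3 | 0.95 | 5.4% | 5.4% | 4.7% |
| Stable 0.4, serial 0.4, noise 0.2 | 0.82 | 6.4% | 6.5% | 5.0% |
| ρ = 0.3 + 0.55·exp(−gap/20) | 0.76 | 7.0% | 7.0% | 5.0% |
| Serial 0.8, noise 0.2, no stable effect | 0.72 | 7.4% | 7.3% | 5.1% |
| Pure decay, 26-week ρ = 0.5 | 0.53 | about 9.8% | 9.3% | 5.2% |
| Pure decay, 26-week ρ = 0.9 | 0.43 | 11.2% | 10.8% | 5.2% |

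The serial parts of the mixed structures use a 26-week correlation of 0.5.

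**Step 3: the wider range.**
- Stable effect plus decay ran from 5.1% to 6.5% over the weights tried, and up to 7.3% in a further set that included rising spread at follow-up.
- Random intercept and slope gave 5.5% to 6.0%.
- Serial correlation and noise with little or no stable effect gave 6.6% to 8.2%.
- Pure decay gave 7.2% to 10.8%, or 6.7% to 10.5% with post-treatment at week 10.
- The mathematical lower limit, ε = 1/4, would give about 15%.

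**Step 4: is spacing the cause?** No. The same unequal gaps with compound symmetry give 5.3%, while equally spaced visits with first-order autoregressive correlation of 0.5 to 0.9 give 6.1% to 8.8%. The cause is correlation that falls with time. The long follow-up makes such a fall likely but does not prove it.

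**The case against.** The strongest objection is that the article never says the test will be uncorrected, and that an epsilon correction is the kind of detail an article leaves to a fuller plan. That stands as far as the correction alone goes: its absence is no error. But the article does choose the model, and the point is that this model suits a schedule of this length poorly when a better one is readily available.

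A reader might infer from the visit spacing that the test necessarily rejects too often, or that the p values of all three primary outcomes are certainly too small. The document does not support this. It gives no correlation or variance pattern for PANSS, mini-ICF-APP or MCCB. The unit treats chronic patients with frequent or long hospital stays, so lasting differences between patients may be large, and these push the structure towards compound symmetry and an inflation of a point or less.

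It is also fair to say that the article does not name treatment-by-time as the deciding effect, that the main effect of treatment does not need sphericity, and that the planned t-tests between arms do not rely on it either. The concern therefore bites only on the effect that expresses a difference in change. With primary outcomes defined largely as change, that is the natural reading of the stated purpose, but it is a reading.

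**Conclusion.** The concern holds in conditional form. The article fixes a model whose treatment-by-time test depends on an assumption that five visits over about 60 weeks make implausible. The consequence is modest in most plausible structures: at a nominal 5%, about 5% to 7% with a stable patient effect, about 7% to 8% with little or none, and up to about 11% only under pure exponential decay. Under compound symmetry there is no inflation.

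These figures rest on 30 patients per arm with complete data, post-treatment at about week 8, assumed covariances, and no correction being applied. They apply separately to each outcome tested in this way. The point merits a change to the plan, but it is not a fatal flaw.

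**What to change.** In the Statistical Analysis section, replace the ANOVA by a linear mixed model for repeated measures with treatment, visit (as a factor) and treatment-by-visit, an unstructured within-patient covariance, and Kenward-Roger degrees of freedom. If the ANOVA is kept, state that all time and treatment-by-time p values use the Greenhouse-Geisser correction, that is, degrees of freedom 8ε̂ and 348ε̂ with 30 complete patients per arm.

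The cost is about one sentence, with no change to design, visits or data collection. The mixed model must estimate 5 × 6 / 2 = 15 covariance parameters, which 90 or more patients can support. The corrected ANOVA gives slightly larger p values and, in the simulations, rejected in 4.6% to 5.3% of null trials.
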